## Discussion

3

Psoriasis vulgaris has a high recurrence rate. The pattern of recurrence varies with each patient. Some patients will have early and frequent recurrence, while others may have long-term remission with few recurrences. Hence, patients may need maintenance treatment for an extended period of time. Psoriasis is characterized by long-term chronic course with recurrent attacks. RCTs that have been previously performed have not provided insights to preventing recurrence. However, real-world studies may have advantages to provide long-term insights. Previous publications have evaluated the clinical efficacy of biological agents for the treatment of psoriasis through retrospective real-world registration studies. However, no real-world or registration studies with regards to TCM for the treatment of psoriasis have been published in China.

This study did not include a placebo group, nor employed a blinded method. Patients in this study included elderly, children, pregnant and breastfeeding women and met the ethical requirements for enrollment in this study. With regard to the study design, we mainly focused on the Psoriasis Longitudinal Assessment and Registry^[21–23]^ (PSOLAR) and the National Central Cancer Registry of China^[24]^ (NCCR). The Psoriasis Registration Platform was designed to demonstrate, train researchers and to strictly adhere to standard operation process. In addition, it included guidelines for strict data collection and a management plan to improve data collection and transfer efficiency. The electronic case registration system is helpful to facilitate the interaction between doctors and patients. It actively monitors and collects information from diverse disease groups to improve data quality and authenticity. Data from the platform can also be easily shared. The platform meets the clinical needs and is reasonably standardize to facilitate the preservation of original medical records. These include access to BMI, PASI, and BSA indicators through an embedded formula. In addition, the platform contains drug library resources, diagnosis and treatment guidelines, to propose individualized prescriptions. Improvements in PASI, BSA and VAS scores for each patient's skin lesions can be visualized and monitored directly.

Based on an intelligent and information-based data collection and data management platform, this study observed and followed-up on thousands of patients within a short period. Data will be analyzed after centralized integration to compare conventional therapy with that of the combination of Chinese and Western medicine treatment. Patients will be evaluated based on recurrence rate 6 months after PASI75, onset time, maintenance time, the incidence of new rashes during treatment and follow-up, World Health Organization Quality of Life Instruments/BSA/VAS scores and treatment costs. The long-term efficacy of TCM in treating psoriasis vulgaris through intelligent and information-based data collection and management will then be established and evaluated. It determined the advantages of TCM and provided real-world evidence for the long-term efficacy of TCM for the treatment of psoriasis. In addition, the platform could evaluate the mode and cost-effectiveness of psoriasis vulgaris treatment in the real world. Improvement of skin lesions, patient quality of life, recurrence rates of skin lesions and the state of anxiety and depression will also be able to be evaluated in the future. Long-term follow-ups of patients during remission and recurrence will provide clues to inducing factors and effective interventions for patient treatment. Using the multicenter registration platform to collect large amounts of standardized data within a short period will help mine and analyze long-term efficacy data of TCM for the treatment of psoriasis from the perspective of recurrence.

Patient management, collection, and analysis of medical data is the aim of the present clinical study. Management of chronic diseases will be investigated using this methodology. Patients will be initially registered using unique codes and then will undergo the relevant examinations based on an standard operation process to ensure consistency. Second, patients will be regularly evaluated for their disease condition by regular follow-up visits. If patients are unable to be physically present, they will be evaluated via online or telephone follow-ups. Third, doctors and patients will have direct access via Wechat IDs managed by research assistants. For common problems, the research assistants will communicate with patients via Wechat to improve patient compliance. Fourth, the database will be regularly checked. Patient treatment plans often change, so it is necessary to review and modify information regularly. Treatments will be evaluated for efficacy and actual benefits of TCM for chronic diseases. After platform establishment, enrollment of patients based on inclusion and exclusion criteria should be strictly followed. Based on preset objectives, there will be different research plans and corresponding statistical analysis required. It will be necessary to hold regular meetings to further develop the platform, share knowledge and data so that investigators can benefit from this platform.

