#### Eligibility criteria

2.3.1

The Inclusion criteria are as follows:

(1)Conform to the diagnostic criteria of Western and Chinese medicine for psoriasis vulgaris.^[16–18]^(2)Study participants will not be selected or excluded until the required number of patients are met to ensure continuous enrollment.(3)Volunteered to participate in the case registration study and signed an informed consent.

The Exclusion criteria are as follows:

(1)Patients with a combination of pre-existing serious systemic diseases, such as cardiovascular, liver, kidney and hematopoietic disease or other primary diseases.(2)Severe mental illness.(3)Patients with poor compliance, inability to communicate and unable to complete the pre-designed registration information.

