#### Non regulatory analysis

2.10.2

For the comparative analysis of 2 groups, qualitative data will be analyzed using the chi-square test, Fisher exact probability, Wilcoxon rank-sum test and CMH chi-square test. Quantitative data in line with normal distribution will be analyzed using *t*-test (homogeneity test of variance between groups, test level at 0.05, and Satterthwaite method will be used for correction when the variance is uneven). Wilcoxon rank-sum test and Wilcoxon signed-rank sum test will be used when the data is abnormally distributed.

The survival analysis will be used to compare statistical significance between the groups (for the appearance of new skin lesions). In addition, the Cox regression model will be used to adjust the impact of baseline PASI values, course of the disease, and body mass index.

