#### Selection of covariates

2.10.4

Covariates will be selected from baseline data or other risk variables affected by treatment. Adjusted analysis will be performed for basic demographic characteristics, body mass index, course of the disease, medical history in the last 3 months, the co-occurrence of psoriatic arthritis, baseline PASI scores, SAS scores, Zung self-assessment of Depression scores, and so on. At the time of patient enrollment to the group. This is to determine if basic conditions between the groups are comparable. Other risk factors will include the use of western medicine (immunosuppressants, biological agents, hormones, antibiotics, and so on).

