#### Efficacy analysis (Adjustment analysis)

2.10.5

Efficacy analysis indicators will include changes in the main efficacy indicators from the initial visit (baseline) to each follow-up period.

Logistic regression analysis will be used to study the relationship between continuous dependent variables and independent variables. Influencing factors will be analyzed to determine which independent variable influences the probability of dependent variable occurrence. The decision analysis method will be used to estimate the probability of each category of the dependent variable (in the presence of a combination of various independent variables), to predict the outcome. The mixed effect of multiple covariates on treatment outcome will be adjusted using the propensity score matching method. First, we will determine if the distribution of patients with similar tendentiousness score is balanced among the groups. The distribution of patients will then be adjusted according to the tendentiousness score to calculate the effect estimation value. Stratified analysis will be conducted based on patients’ PASI score which will be divided into 4 groups based on the 4 levels of PASI score (less than 10,10–20,20–30 and more than 30).

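### The Cox model for new skin lesions has no age term although children are enrolled, and no covariate list names pregnancy or breastfeeding, so some residual confounding of the cohort comparisons is possible

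*Protocol article*

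**What the plan says.** The Discussion describes a broad population: "Patients in this study included elderly, children, pregnant and breastfeeding women and met the ethical requirements for enrollment in this study". Section 2.3.1 fits this. It sets no age or pregnancy limit and asks for consecutive entry: "Study participants will not be selected or excluded until the required number of patients are met to ensure continuous enrollment". Section 2.3.2 assigns patients to the TCM, conventional or integrated cohort by the treatment they actually received.

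The adjustment is described in three places.

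- Section 2.10.2, for the appearance of new skin lesions: "the Cox regression model will be used to adjust the impact of baseline PASI values, course of the disease, and body mass index". This list has no open ending.
- Section 2.10.4, the general covariate plan: "Adjusted analysis will be performed for basic demographic characteristics, body mass index, course of the disease, medical history in the last 3 months". It goes on to psoriatic arthritis and "baseline PASI scores, SAS scores, Zung self-assessment of Depression scores, and so on".
- Section 2.10.5, for efficacy: "The mixed effect of multiple covariates on treatment outcome will be adjusted using the propensity score matching method". Balance is to be checked first. The only stratification stated is by four PASI levels.

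On BMI, the Discussion says only that the platform offers "access to BMI, PASI, and BSA indicators through an embedded formula". The formula is not given.

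**The concern.** In a cohort defined by treatment received, any patient feature that affects both the treatment chosen and the outcome has to be in the adjustment. Childhood, pregnancy and breastfeeding are plausible features of this kind, and the article says such patients are enrolled.

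The Cox list in section 2.10.2 omits age but includes BMI. If children have lower BMI than adults, a single BMI coefficient estimated mainly in adults assigns children a low predicted hazard because they are children, not because they are lean for their age. A cohort with more children then looks worse than it is, even if children do no worse than adults. If their risk also differs, the distortion changes further.

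For the main outcome the gap is narrower. Age is plausibly within the demographics of section 2.10.4, but pregnancy and breastfeeding are not named. At stake is a shift in the estimated cohort difference that reflects who the patients are rather than how they were treated.

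**Working it through.** **1. The plan's own figure.** Section 2.7 assumes recurrence of 73.7% (conventional), 28.6% (integrated) and 20% (TCM), α = 0.05, power 0.80. Testing is two-sided (section 2.10.1). The smallest contrast is 28.6% against 20%, a difference of 8.6 points. With pooled variance and mean proportion 0.243:

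n = [1.960 × √(2 × 0.243 × 0.757) + 0.842 × √(0.286 × 0.714 + 0.20 × 0.80)]² / 0.086² = 389.3, rounded up to 390.

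This matches the stated 390 per group, so 8.6 points is a fair yardstick. The planned 507 per group with 30% loss leaves 507 × 0.70 = 354.9, about 355 evaluable. Step 3 uses that number.

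**2. Main outcome, before any adjustment.** If a subgroup makes up share f₁ of one cohort and f₂ of another, and its recurrence risk differs from other patients' risk by d, the spurious risk difference is (f₁ − f₂) × d. The article gives none of these values. Assumed: 10-15% in one cohort, 3-5% in the other, d of 10 to 30 points.

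- Smallest: (0.10 − 0.05) × 0.10 = 0.005, or 0.5 points.
- Largest: (0.15 − 0.03) × 0.30 = 0.036, or 3.6 points.
- Against 8.6 points: 0.5/8.6 = 6% and 3.6/8.6 = 42%.
- Against the TCM-conventional contrast, 73.7 − 20 = 53.7 points: 3.6/53.7 = 7% at most.

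These are ceilings for an unadjusted analysis. Matching on age and other covariates would remove part of the distortion.

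**3. Cox model.** Simulated under assumptions: 355 per cohort; 15% against 5% children; adult BMI mean 24.5, SD 3.8; child BMI mean 17, SD 2.5; hazard ratio 1.25 per SD of age-standardised BMI; true cohort hazard ratio 1.00. Run A used a baseline hazard of 0.12 per month over 12 months (400 runs, Monte Carlo standard error about 0.004). Run B used follow-up giving roughly 60% events (300 runs).

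| Adjustment | Run | Child hazard equal | Child hazard 1.5 times |
|---|---|---|---|
| BMI, no age | A | 1.03 | 1.06 |
| BMI, no age | B | 1.02 | 1.05 |
| BMI + linear age | B | 1.02 | 1.04 |
| BMI + child indicator | B | 0.99 | 0.99 |
| BMI-for-age + child indicator | B | 0.99 | 0.99 |

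In run A, adding a child term also returned 1.00. Three things follow.

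- Omitting age biases the cohort estimate even when children have the same risk.
- The child term removes the bias. Changing the BMI scale adds nothing further to the cohort estimate, and a straight-line age term removes only part of the bias.
- The bias is small: ln(1.02) = 0.020 to ln(1.06) = 0.058, against a standard error of about 0.09 on the log scale, so roughly 0.2 to 0.65 of a standard error.

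Pregnancy was not simulated.

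**The case against.** The strongest defence is that this is a condensed article. Section 2.10.4 already lists demographics and recent medical history and ends openly. Age falls naturally under the first, and pregnancy could fall under the second or the open end. Propensity matching with a balance check covers the main outcome. The Cox model serves a secondary outcome, and section 2.10.4 may be meant to widen its covariates too. Final coding of covariates is commonly left to an analysis plan. Most of this stands, and it confines the point to possible residual confounding outside the Cox model. It does not remove the Cox point: section 2.10.2 states a specific list without age, and nothing in the article says that the wider list replaces it.

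A reader might infer two stronger things. The first is that unstandardised BMI is used for everyone, so that the adjustment for overweight is wrong in children and pregnant women. The article does not show the formula, and the simulation shows that the BMI scale does not drive the cohort bias once children are identified. The second is that treatment choice by age or pregnancy does confound the main comparison. No section says how age or pregnancy steers treatment, how many such patients there are, or how their recurrence differs. It is a plausible risk and no more.

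**Conclusion.** The point holds in limited form. The listed Cox covariates omit age in a non-randomised cohort that includes children, and this can leave age-related confounding in the analysis of new lesions. Pregnancy and breastfeeding are not named for the propensity-matched comparison, so residual confounding there is possible but not shown.

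The size cannot be known from the article. The 0.5 to 3.6 points rests on assumed shares and risks and applies before adjustment. It matters mainly for the 8.6-point TCM-integrated contrast and little for the 53.7-point TCM-conventional one. The Cox bias of about 1.02 to 1.06 rests on an assumed threefold imbalance in children and stays under one standard error. This is a worthwhile refinement, not a threat to the study's main conclusion.

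**What to change.** - Section 2.10.2: add age to the Cox model in a form that separates children from adults, either a child indicator or a non-linear age term. This agrees with the demographics already listed in section 2.10.4. A linear age term alone is not enough.
- Sections 2.10.4 and 2.10.5: include pregnancy or breastfeeding at enrolment in the propensity score where it is recorded.
- Add a sensitivity analysis that repeats the main comparison in adults who are neither pregnant nor breastfeeding.

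BMI-for-age in children is optional; it mainly makes the BMI coefficient easier to interpret. Exact matching on these groups is not needed, and neither is pre-pregnancy BMI, which the article does not show to be collected.

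The cost is a few lines of analysis text. Age should already be available with the demographics. Pregnancy status may need a data field, since the content of the data collection schedule could not be seen. The restricted analysis will be slightly less precise.

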## Abbreviations

Abbreviations: BSA = body surface area, PASI = psoriasis area and disease severity index score, SAS = Zung self-rating Anxiety Scale, TCM = traditional Chinese medicine, VAS = visual analog scale of Psoriasis skin itch score.
